The above mentioned fields of surgery are all based on the rather fixed positions of the bone and soft tissue components. Retroperitoneal organs, *e.g.* kidney, adrenal glands and iliac vessels can also be considered as relatively fixed and are therefore accessible targets for navigation surgery using preoperative images. Adrenalectomies were performed in a pilot setting using a laparoscopic navigation system^10. Video overlay of reconstructed three-dimensional CT-images onto real-time laparoscopic footage was successfully tested in laparoscopic nephrectomies.

A technically more challenging field for surgical navigation is the abdomen. Organ movement, breathing motion and tissue deformation make the maintenance of accurate anatomical representation during the procedure very complex. More importantly, intra-abdominal targets such as colon or rectum tumors often do not have a fixed position. To accomplish real-time surgical navigation in the presence of “moving targets” a novel surgical tracking and navigation system needs to be developed.

---

There are two main technical options for surgical tracking systems. The first is optical tracking, which is based on a set of 2D or 3D camera's which can be used to detect active or passive markers on the patient and on surgical instruments. Secondly, electromagnetic (EM) tracking can be used, which is based on a magnetic field generator and EM-sensitive sensors. The position of a sensor in the magnetic field is associated with generation of a specific current, revealing the sensor position. Optical tracking systems are known for their accuracy, which is sub-millimeter, but they are dependent on a direct line-of-sight between the camera's and the markers in order to provide positional information. Due to the nature of magnetic fields, EM-navigation systems do not depend on a line-of-sight, while the systems have an accuracy of 1-2 mm. A further challenge for EM systems is the influence of ferromagnetic material on the stability of the generated magnetic field.

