In our project we aim to develop a navigation system for colorectal cancer surgery which gives us real-time information on the position and orientation of the tumor. Simultaneously, the system will also be used to visualize and localize organs at risk with respect to the tumor. Since the tumor is not visible during the majority of surgical procedures, the use of optical tracking systems is limited. We are developing and implementing a surgical image-guided EM navigation system in which traceable sensors are implanted in or near the tumor to provide the surgeons with real-time information on the tumor location and orientation. Reference sensors, which are placed on the patient surface during acquisition of preoperative scans, are used during surgery to relate the imaging information to the actual patient position during surgery. Organs at risk which are relatively rigid with respect to the reference sensors, such as the iliac vessels and a large part of the ureters, can be located using the reference sensors. This is also valid for pathologic lymph nodes which are located near the large vessels, as well as for tumors which are rigid due to invasion of pelvic structures. The final system with implanted sensors in the tumor will provide accurate information on tumor position and extent for radical resections independent of the mobility of the tumor, and simultaneously, better insight in organs at risk for reduced morbidity.

The aim of this project is to gain first experience with the electromagnetic navigation system and its application during abdominal surgery. This first step encompasses the evaluation of the feasibility and safety of the system. Furthermore, the accuracy of the system to identify anatomical landmarks and structures with a relatively fixed position, such as iliac vessels, ureters, and fixed tumor deposits is assessed.

---

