#### Preparation:

- One day before surgery a contrast-enhanced CT-scan of the pelvis and abdomen is performed. During the scan three removable electromagnetic marker-patches are placed on the skin at superficial bony structures of the pelvis, such as the anterior superior iliac spine. Locations will be marked precisely with a permanent marker.
- Segmentations and three-dimensional reconstructions are made of the pelvic bone, the iliac vessels, ureters, the tumour, and pathologic lymph nodes using the CT-scan.
- The resulting 3D reconstructions are evaluated by the surgeon who will perform the surgical procedure.

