#### In the OR:

- In the OR the patient will be placed on the table according to standard protocol, with the exception that the EM field generator will be placed between the table and the patient (Fig. 1).
- The marker-patches will be positioned at the scan locations and the navigation system will be calibrated.
- The 3D reconstructions will be loaded into the navigation software.
- An intra-operative XPerCT (no contrast fluid used) is acquired to assess the actual patch positions with respect to the 3D model. The XPerCT is used to improve the navigation accuracy.
- Before surgeons start applying the sterile field, an estimate of the registration accuracy between the CT and actual marker positions will be performed. If tolerance limits are exceeded, the navigation procedure during surgery will be cancelled.
- At the moment the laparotomy is advanced to the stage in which the iliac vessels are visible for the surgeon the study measurements are started.
- After the measurements the surgeon will proceed with the standard surgery. If the tumour is rigid, or pathologic lymph nodes are present around the large vessels, the navigation system can be used to localize them.

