#### Actual measurements:

- First the surgeon will point the blunt tip probe at the bifurcation of the aorta into the left and right common iliac artery, and also both bifurcations into the internal and external iliac artery. These measurements will be performed without direct

visualization of the navigation system to the surgeon. For each pointed position the estimated position on the navigation system will be stored.

- In the second part, the surgeon will use the navigation system and the probe to localize the ureters. These are generally not visible for the surgeon. The resulting location of ureter tracts will be visually assessed by the surgeon in terms of trueness.

Total time of the proposed preparation and measurements during the surgical procedure will take no longer than 20 minutes. Extra time needed to use the navigation system during surgery will be recorded.

Specific participation for the patient in the study ends during the operation after the measurements have been performed.

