## **8. STATISTICAL ANALYSIS**

### **8.1 Descriptive statistics**

In this registration study, distances will be measured between the estimated probe positions with respect to the bifurcation of the common iliac artery into the left and right artery, both bifurcations into the internal and external iliac artery and ureters. Measurements will be compared within patients to assess patient specific systematic errors, and between patients to assess system specific systematic errors. Due to the nature of a registration study, significance can not be estimated. However, usability and subjective assessment of experience by the surgeons will be valuable for future projects. Assessment of the ureter tracts will be based on the surgeon's opinion, and scored in terms of excellent, reasonable, dubious or wrong. Actual assessment of tumour boundaries and suspected lymph node locations will be recorded and cross-referenced with pathology

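### All blind accuracy points lie on arteries in the opened abdomen, so any vessel displacement they share cannot be separated from system or registration error in section 8.1

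*Protocol*

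**What the plan says.** Protocol 5.1 (Actual measurements) fixes the first blind reading: "First the surgeon will point the blunt tip probe at the bifurcation of the aorta into the left and right common iliac artery". The other two lie lower, one on each side of the body: "and also both bifurcations into the internal and external iliac artery". That makes three points, all on arteries. Section 6.1 makes the distance from the probe to these bifurcations in the model the objective yardstick for accuracy.

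On timing, 5.1 (In the OR) says: "At the moment the laparotomy is advanced to the stage in which the iliac vessels are visible for the surgeon the study measurements are started". The reference model comes from the CT of the day before: "Segmentations and three-dimensional reconstructions are made of the pelvic bone, the iliac vessels, ureters, the tumour, and pathologic lymph nodes using the CT-scan". The pelvic bone is therefore in the model, but no bony point is probed. The intra-operative scan serves another purpose: "An intra-operative XPerCT (no contrast fluid used) is acquired to assess the actual patch positions with respect to the 3D model". It is listed before the check made ahead of the sterile field.

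Section 8.1 names two sources for the measured distances: "Measurements will be compared within patients to assess patient specific systematic errors, and between patients to assess system specific systematic errors".

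On tissue movement, the introduction says of the abdomen: "Organ movement, breathing motion and tissue deformation make the maintenance of accurate anatomical representation during the procedure very complex". It also treats some targets as locatable from the surface sensors: "Organs at risk which are relatively rigid with respect to the reference sensors, such as the iliac vessels and a large part of the ureters". Section 4.4 says the study is needed to estimate how the operating-room environment affects the system.

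**The concern.** The bifurcation distance combines at least three things: error of the tracking system, error of the patch registration, and any movement of the vessel between the CT and the reading in the opened abdomen. Section 8.1 provides for system-specific and patient-specific error and does not mention the third. A displacement typical of laparotomy would enter the between-patient mean and be read as system error. One that differs between patients would be read as patient-specific error.

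The remedies differ. A tracking or registration fault calls for work on the system. Target movement calls for tracking the target, which the introduction foresees with implanted sensors. A study meant to evaluate and improve the system, and to estimate environmental influence on it, should not attribute one to the other. The relative rigidity of the vessels is also the premise of the surface-marker method, and no planned step tests it directly after opening.

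**Working it through.** The plan states no figure for this point, so there is none to reproduce. All millimetre values below are assumptions unless a source is given.

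**1. Which readings could separate the sources?**

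| Reading | Site | When | Screen hidden |
|---|---|---|---|
| Three bifurcations (5.1, 6.1) | artery | after opening | yes |
| Ureters (5.1) | soft tissue | after opening | no |
| Rigid tumour or nodes, if present (5.1) | varies | after opening | no; 8.1 cross-references with pathology |
| Each reference sensor (5.2) | skin | before opening | no, visual, 0.5 cm |
| Belly button (5.2) | skin | before opening | no, visual, 1.0 cm |
| CT versus XPerCT patch position (6.1) | skin patches | before opening | not a probe reading |

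Blind points after opening: three on arteries, none on bone.

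**2. What the planned comparisons estimate.** Along one axis, for patient i and point j:

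y_ij = b + r_i + D_i + d_ij + e_ij

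Here b is system bias; r_i is registration error (SD σr); D_i is displacement shared by the three points (mean δ, SD σD); d_ij is its point-specific part (SD σd); and e_ij is pointing noise (SD σe).

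- Between-patient mean: b + δ
- Patient-specific SD: √(σr² + σD²)
- Within-patient SD: √(σd² + σe²)

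Only the sums can be estimated. More patients or repeated pointing do not split b from δ.

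**3. Numbers.** Assume b = 0, σr = 2 mm, σe = 1 mm, σD = δ/2 and σd = δ/4.

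| δ (mm) | Apparent system error | Patient SD | Within-patient SD |
|---|---|---|---|
| 0 | 0 | √4 = 2.0 | √1 = 1.0 |
| 2 | 2 | √(4+1) = 2.2 | √(1+0.25) = 1.1 |
| 5 | 5 | √(4+6.25) = 3.2 | √(1+1.56) = 1.6 |
| 10 | 10 | √(4+25) = 5.4 | √(1+6.25) = 2.7 |

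A simulation of 20,000 patients agreed to within 0.1 mm. With the same spread of displacement, b = 5 with δ = 0 and b = 0 with δ = 5 both gave mean 5.0, patient SD 3.2 and within-patient SD 1.6 mm.

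**4. Effect on a root-mean-square distance.** If displacement d is independent of the true error r, the reported value is √(r² + d²).

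| r (mm) | d = 1 | d = 3 | d = 8 |
|---|---|---|---|
| 1 (order of field-generator accuracy, 5.2) | 1.4 | 3.2 | 8.1 |
| 5 (assumed) | 5.1 (+2%) | 5.8 (+17%) | 9.4 (+89%) |
| 10 (registration RMS limit, 5.2) | 10.0 (+0.5%) | 10.4 (+4%) | 12.8 (+28%) |

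The first row takes field-generator accuracy as the whole error, which is optimistic. The last row borrows a limit on sensor residuals, which is not itself an error at the vessel.

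**5. What the stored positions can show.** Take the registration to be rigid; the protocol does not use the word, but describes matching sensor positions and judging the residuals. Before noise, the measured position is R(x_j + v_j) + t, with x_j the CT position, v_j the vessel displacement, R a rotation and t a shift. The distance between points j and k is then |x_j − x_k + v_j − v_k|. R and t drop out, so a difference from the CT distance points to unequal displacement. If v_j = v_k the distance is unchanged and the shared displacement stays hidden. With σe = 1 mm per reading, noise along the line joining two points has SD √2 = 1.4 mm.

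**6. Limit of a bone reading.** In the simulation, three bone points per patient recovered b and δ, but only because bone and artery were given the same registration error. In practice that error varies with location: an assumed rotation of 2 degrees over 10 cm gives 100 mm × tan 2° = 3.5 mm with no tissue movement.

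**The case against.** The protocol picks the bifurcations because it regards them as good targets: the introduction calls retroperitoneal structures, the iliac vessels among them, relatively fixed. It does not name deformation as the main difficulty; it ranks the lack of a fixed position of colon and rectal tumours as more important. Readings begin when the vessels become visible and standard surgery continues afterwards, so much of the dissection comes later. The sensor checks, the phantom test of the whole chain and the CT-versus-XPerCT comparison give some evidence on the rigid component. Distance at the vessel is also the quantity the study sets out to describe, in a descriptive proof-of-principle study.

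Most of this stands. It lowers the likely size of the problem and supports keeping the bifurcation distance as the main accuracy measure. It does not supply a rigid reading after opening, and it does not justify the two-way labelling.

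A reader might infer that the data are blind to deformation and that every excess millimetre would be called system or patient error. That is not supported. Displacement that differs between the three points appears as within-patient scatter and as changed inter-bifurcation distances. A reader might also expect a bone comparison on the XPerCT to settle the matter. That scan is listed before opening, so it cannot show later displacement, and such a comparison would largely repeat the patch comparison already planned in 6.1.

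**Conclusion.** The point holds for displacement shared by the three bifurcations. That part is fully confounded with system or registration error under the planned comparisons, and 8.1 would report it under one of those labels. This follows from the measurement plan and needs no assumed figure.

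The size is unknown. With a true error of 5 mm, an assumed displacement of 1 to 8 mm inflates the reported value by 2% to 89%; with 10 mm, by 0.5% to 28%. With vessels as fixed as the introduction supposes, the effect may be negligible. The documents do not support the stronger reading that reported accuracy will be substantially wrong, or that the accuracy measure is invalid. As total error at the target it remains sound.

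The change is worth making because it is cheap and alters what can be concluded about the system. An analysis plan could correct the labels, but it cannot recover a bone reading that was never stored.

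**What to change.** - **Section 8.1, wording.** Describe the bifurcation distance as total target error, including any tissue displacement. Do not label its between-patient mean as system error alone.
- **Sections 5.1 (blind part) and 6.1, one reading.** Store one additional position at a segmented bony pelvic point near the bifurcations, only where it is already reachable without extra dissection. Report bone and bifurcation errors side by side as vectors. Treat their difference as an indication of tissue displacement and not a pure measure of it, because registration and field errors vary with location.
- **Section 8.1, one analysis.** From the stored positions, compare the three inter-bifurcation distances with those in the CT model, and state that this detects unequal displacement only.

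The wording and the analysis use data already planned. The bone reading costs seconds of probe time, which should count within the 20-minute limit. It will be missing where no bone is reachable; the protocol does not say how often bone is exposed when measurements start, so report the number of patients with a bone reading. No extra patients or scans are needed.

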This is a registration study to evaluate the overall performance, safety and potential benefit of the surgical navigation system during abdominal surgery. The surgeons are aware of the experimental setup, and are therefore responsible for the navigation interpretation and actions. The eventual goal of this project is to judge the potential use of the navigation system for further clinical studies. When the system proves safe and accurate, further studies will be directed to improve tumor free surgical resection margins in abdominal surgery as well as to reduce the morbidity rate by more selective resections sparing more healthy tissue by intra-operative navigation.

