### Primary Objective:

Feasibility and safety of an in-house developed electromagnetic navigation system during abdominal surgery.

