### **4.4 Sample size calculation**

This project is a proof of principle study. The goal is to assess feasibility and safety of the electromagnetic navigation system in a clinical environment during surgery. The system is already extensively tested in a non-clinical setting and has shown to be highly accurate. Pre-clinical tests within the OR have shown that some environmental changes might influence the accuracy of the system. However, assessing all combinations of possible environmental changes is impossible. We have to perform this registration study to have an estimate of the expected environmental influences during surgery.

During the course of the study, we have identified an import application for navigation; i.e. locally advanced T3 or T4 rectal tumour and tumour recurrences in the abdomen and pelvic area. Lately, due to logistic reasons (OR planning), the drop-out of patients who signed informed consent was higher than expected. In order to obtain sufficient accuracy measurements to obtain statistical relevant numbers in this study, 20 more patients should be included. This accounts for 15 successful measurements and 30% chance of failure.

---

Inclusion of maximally 95 patients will be sufficient to evaluate and improve the system during abdominal surgery. No sample size calculation is performed.

---

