### Main endpoint

In this study we aim to evaluate the feasibility and safety of the navigation system by identifying the iliac vessels and ureters.

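### Section 8.1 wrongly treats the registration design as a bar to statistical inference; a single-group study supports confidence intervals, and the protocol's own aims need them

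*Protocol*

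**What the plan says.** The primary objective is "Feasibility and safety of an in-house developed electromagnetic navigation system during abdominal surgery", and section 6.1 gives the main endpoint as "In this study we aim to evaluate the feasibility and safety of the navigation system by identifying the iliac vessels and ureters". No rate, threshold or margin is attached to either. Accuracy is a secondary objective.

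Section 8.1 describes the distances between probe position and arterial bifurcations, and a comparison of these within and between patients to separate patient-specific from system-specific systematic error. It then says: "Due to the nature of a registration study, significance can not be estimated". A four-level surgeon score for the ureters and a cross-reference to pathology follow. Section 8.1 does not say how safety or feasibility will be summarised, and it neither plans nor excludes confidence intervals.

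Three other places bear on the point:

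- Section 4.4 justifies 20 more patients as needed "to obtain statistical relevant numbers in this study". It also says "Inclusion of maximally 95 patients will be sufficient to evaluate and improve the system during abdominal surgery" and "No sample size calculation is performed".
- Section 6.1 has the patches registered with both the pre-operative CT and the XPerCT position, so that the improvement can be assessed.
- The Summary, under burden, risks and benefit, says: "The eventual goal of this project is to judge the potential use of the navigation system for further clinical studies". It continues: "When the system proves safe and accurate, further studies will be directed to improve tumor free surgical resection margins".

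**The concern.** A registration design limits what can be compared, since there is no control group. It does not prevent sampling uncertainty from being quantified, and it does not prevent a test where a within-patient contrast exists. Section 8.1 therefore gives a false reason for having no inference, and anyone writing a later analysis plan would have to override it.

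What is at stake is how the result is read. Sections 6.4 and 7.2 end the study if a serious adverse event possibly related to it occurs. A study that runs to completion will therefore report about zero such events almost by construction. The count then says little, and the upper confidence limit carries the information. If the Summary's condition for moving on is judged from the count alone, readers are not told what event rate the data still allow.

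**Working it through.** **The plan's own figure first.** Section 4.4 gives 20 extra patients for 15 successful measurements and a 30% chance of failure. 15 × 1.3 = 19.5, rounded up to 20, reproduces it. The usual inflation, 15 / (1 − 0.30) = 21.4, gives 22. The maximum of 95 has no calculation behind it.

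**Inputs.** Maximum n = 95, single group (4.4, 6.2); 15 successes in 20 and 30% failure, both stated for the extension only (4.4). The protocol states no alpha, margin, SD or intra-patient correlation. I use two-sided 95% intervals throughout.

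**Safety, zero related events.** The exact (Clopper-Pearson) upper limit is 1 − 0.025^(1/n).

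- n = 95: 1 − 0.025^(1/95) = 3.8%.
- n = 66: 1 − 0.025^(1/66) = 5.4%. Here 66 is 0.70 × 95 = 66.5, rounded down. Applying the extension's 30% to all 95 patients is an assumption.
- One event in 95 would give 0.03% to 5.7%.

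The same point from the other side: with a true rate of 1%, the chance of seeing no event is 0.99^95 = 38% in 95 patients and 0.99^66 = 52% in 66. An empty event list is weak evidence on its own.

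**Feasibility.** With 15 successes in 20, the estimate is 75% and the exact 95% interval 50.9% to 91.3%.

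**Mean target error.** With one value per patient the 95% half-width is t(0.975, n−1) / √n in SD units: 0.20 SD at n = 95, 0.25 SD at n = 66 and 0.55 SD at n = 15. Up to three bifurcations are pointed at in each patient, so the values are not independent. With m = 3 points and intra-patient correlation ρ, an analysis that ignores clustering understates the standard error of the mean by √(1 + (m − 1)ρ). This is 1.00 at ρ = 0, √2 = 1.41 at ρ = 0.5 and √3 = 1.73 at ρ = 1. The correlation is not given, but section 8.1 itself looks for patient-specific systematic error, which would make ρ positive.

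**The aims set against the sentence.**

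| Aim in the protocol | What it needs |
|---|---|
| Systematic error within and between patients (8.1) | A standard error or interval, to tell systematic error from scatter |
| Improvement from XPerCT over pre-operative CT (6.1) | A paired within-patient interval; no control group needed |
| More patients for statistical reasons (4.4) | A precision for which the number matters |
| Proof of safety and accuracy before further studies (Summary) | A statement of what the data exclude |

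All four are available in this design.

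**The case against.** The strongest reply is that the sentence speaks of significance, not of confidence intervals, and that interval methods may sit in a statistical analysis plan that is not shown. That is right as far as it goes. A reader might infer that safety and feasibility will be reported with no error bars. The documents do not support this: section 8.1 does not exclude intervals, and the sentence follows the accuracy distances, a secondary objective. A later plan can add intervals, but it cannot make the stated reason true.

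A reader might also infer that the protocol intends to declare the system safe. The Summary states a condition for later studies, and the stated goal is to judge potential use; handling, usability and extra time count as well. The word chosen for that condition is nonetheless strong for a descriptive study with no stated uncertainty.

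It can be said that wanting enough accuracy measurements is compatible with planning no test, so the clash with section 4.4 is not a flat contradiction. I accept that: the two passages sit badly together, no more.

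Finally, it is tempting to set the upper limit against the ureteric damage incidence quoted in section 1. That comparison is not like for like. The quoted incidence is surgical damage in published series, whereas the limit concerns events related to the device, and section 5.2 confines the probe to visible, approachable regions.

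**Conclusion.** The point holds in this limited form: section 8.1 gives a wrong reason for having no inference, and the Summary's condition for moving on has no uncertainty attached to it. With no related event, the data would still allow a rate of up to 3.8% (95 patients) or 5.4% (66 patients). Feasibility of 15 in 20 would be compatible with anything from 51% to 91%.

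The 3.8% assumes that all 95 patients are included and exposed. The 5.4% rests on applying the extension's 30% to everyone, and that 30% follows a remark on logistic drop-out, so it may not be a technical failure rate. The limits describe a study that completes without an event; one that stops at its first related serious event would need an interval that reflects the stopping. Intervals of this kind measure sampling uncertainty only and do not supply a comparison with surgery without navigation. Because the protocol states no alpha, margin or threshold, no formal test can be called wrong.

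**What to change.** Replace the sentence in section 8.1 with wording such as:

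> No hypothesis test is planned. The proportion of patients with a completed navigation measurement and the proportion with a device-related event are reported with exact two-sided 95% confidence intervals, target error with a 95% confidence interval clustered by patient, and the CT versus XPerCT difference with a paired 95% confidence interval.

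State the denominator of each proportion in the same place. Section 6.3 withdraws patients in whom technical problems prevent measurement, and a feasibility proportion that left them out would be flattered.

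In the Summary, replace the claim of proof with wording tied to these intervals, for example that zero related events in 95 patients would give a two-sided 95% upper limit of 3.8%.

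The cost is a few sentences, slightly more analysis and a more modest safety statement. No procedure, sample size or clinical rule changes.
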